### Secondary efficacy analysis: multifocal VEP

The secondary (electrophysiology) outcome measure is the change in MF-VEP latency, between baseline and week 26, for those eyes with delayed (≥ 151 ms) latency at baseline. Eligible eyes will additionally have RNFL thickness ≥ 70 μm and ≥ 28/56 recordable segments (see outcomes Sect. 12 for the definition of eligible eyes). This will apply the same statistical analyses as for the primary outcome measure with the dependent variable replaced by the change in MF-VEP latency.

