### Primary outcome measure: full-field VEP

The primary analysis of this trial will compare the mean change in the P100 latency of the full-field VEP from baseline and week 26, between metformin + clemastine (research arm) and placebo (control arm). This will be based on eligible eyes with delayed (≥ 118 ms) baseline P100 latency. Eligible eyes will additionally have RNFL thickness ≥ 70 μm (see outcomes Sect. 12 for the definition of eligible eyes). A mixed-effect model will be used for eyes nested within participants, with random effects for participants and fixed effects for treatment allocation at randomisation, baseline P100 latency and stratification factors.

Fixed effects: treatment allocation, baseline P100 latency, age at consent (≤ 40 years vs > 40 years), sex (male vs female), baseline MS DMT treatment category (1 vs 2) [5], screening EDSS (≤ 4.0 vs > 4.0).

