### Secondary efficacy analysis: change in lesional MTR

The secondary (MRI) outcome measure is the change in lesional MTR, between baseline and week 26, for the lesions stratified by location or by tissue-specific cohort baseline lesional MTR values.

Analyses will be presented for change in lesional MTR for MS lesions grouped according to each location as follows: periventricular, deep white matter, juxtacortical, leukocortical, cortical grey matter, deep grey matter, mixed deep grey matter and white matter, brainstem and cerebellar lesions. Based on previous research [27], we hypothesise that the clearest effect will be seen in grey matter and brainstem lesions. We will apply the same method as applied for the primary outcome measure, with the dependent variable replaced by the change in lesional MTR for each lesion location subgroup. An interaction term will compare treatment group differences between lesion locations.

Analyses of change in lesional MTR stratified by cohort baseline lesional MTR values will be applied using the same method as the primary outcome measure with the dependent variable replaced by the change in lesional MTR for lesions: (1) grouped as being above or below the cohort median lesion MTR and (2) grouped into quartiles based on the baseline cohort lesion MTR. In line with previous research [27], the interaction test between treatment effects in different lesional groups will be a variable of key interest.

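### The MF-VEP and lesional MTR models are defined by replacing the outcome of the primary model, and nothing replaces its baseline P100 latency covariate

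*Protocol article*

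**What the plan says.** The section on the primary outcome measure (full-field VEP) sets out the model in full. Its structure is "A mixed-effect model will be used for eyes nested within participants, with random effects for participants". Its covariates begin "Fixed effects: treatment allocation, baseline P100 latency" and continue with the four stratification factors. The baseline term is named as P100 latency, not generically as the baseline of the outcome.

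The two secondary efficacy sections define their models by reference to this one:

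- Multifocal VEP: "This will apply the same statistical analyses as for the primary outcome measure with the dependent variable replaced by the change in MF-VEP latency". Eyes enter on a threshold of this test's own: "for those eyes with delayed (≥ 151 ms) latency at baseline".
- Lesional MTR by location: "We will apply the same method as applied for the primary outcome measure, with the dependent variable replaced by the change in lesional MTR", fitted for each location subgroup, with an interaction term to compare locations.
- Lesional MTR by baseline MTR: "using the same method as the primary outcome measure with the dependent variable replaced by the change in lesional MTR for lesions" split at the cohort median or into quartiles of baseline lesion MTR.

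The section on additional analyses {20b} sends VEP amplitude, acuity, colour vision, visual fields and OCT to the method of the primary analysis. It does not use the replacement wording.

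**The concern.** Each secondary section says what is exchanged, and each time it is the response. An analyst following the text would regress change in MF-VEP latency, or change in lesional MTR, on baseline P100 latency and would leave out the baseline of the outcome itself.

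For MF-VEP that model can be run but is inefficient. P100 comes from a different test, and the section on the multifocal VEP outcome argues that full-field VEP often misses small, localised demyelination. Eyes are also selected on a threshold of baseline MF-VEP latency, which invites regression to the mean. That affects both arms alike on average, but a chance difference between the arms at baseline would carry over into the comparison of change.

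For MTR the literal model cannot be run without a further decision. P100 belongs to an eye and MTR to a lesion. The sample size section reports that around half of participants had only one eligible eye, so many of the others have two P100 values and no rule says which a lesion receives. Nesting eyes within participants has no meaning for brain lesions either. Yet the section on the MTR outcome justifies these analyses by the dependence of remyelination on how demyelinated a lesion is at baseline.

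**Working it through.** **1. The plan's own figure.** With a difference of 3.0 ms, SD 5 ms, two-sided 5% and 80% power, the normal approximation gives 44 eyes per arm and the t-test gives 45 (power 0.804; 0.795 at 44). Allowing 10%: 45/0.9 = 50. The sample size statement reproduces, and nothing below alters it.

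**2. Reading the sections together.**

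| Element | Primary | MF-VEP | MTR |
|---|---|---|---|
| Response | change in P100 latency | replaced | replaced |
| Baseline covariate | P100 latency | none named | none named |
| Unit | eye | eye, own threshold of 151 ms | lesion |
| Nesting | eyes in participants | carried over | carried over, does not fit |
| Own baseline elsewhere | – | entry threshold only | none by location; median or quartile group in the second analysis |

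**3. Size of the precision loss.** The documents give no correlations and no SD for MF-VEP or MTR change, so this is an illustration on assumed values. Let r be the absolute correlation of own baseline with change, and ρ the correlation of own baseline with baseline P100. Assume that P100 predicts change only through own baseline, and ignore clustering and the truncation at 151 ms. The residual variances, as fractions of the variance of change, are:

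- own-baseline adjustment: 1 − r²
- P100 adjustment: 1 − (rρ)²
- variance ratio, own to P100: (1 − r²) / (1 − r²ρ²)

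| r | ρ = 0 | ρ = 0.3 | ρ = 0.6 | ρ = 0.8 |
|---|---|---|---|---|
| 0.2 | 0.96 | 0.96 | 0.97 | 0.99 |
| 0.3 | 0.91 | 0.92 | 0.94 | 0.97 |
| 0.5 | 0.75 | 0.77 | 0.82 | 0.89 |
| 0.7 | 0.51 | 0.53 | 0.62 | 0.74 |

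Example: r = 0.5, ρ = 0.8 gives 0.75 / (1 − 0.25 × 0.64) = 0.75 / 0.84 = 0.89.

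**4. Which rows are plausible.** If baseline and follow-up have equal variance and correlation c, then r² = (1 − c)/2, so c = 1 − 2r². The rows r = 0.2, 0.3, 0.5 and 0.7 correspond to c = 0.92, 0.82, 0.50 and 0.02. A highly repeatable measure therefore sits in the upper rows, where the gain is small. The bottom row is an extreme case under equal variances.

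**5. Chance imbalance.** Under the same equal-variance assumption, a chance difference D between arms in own baseline shifts an unadjusted change by about −(1 − c)D. Adjusting for P100 removes only the part of D that the P100 difference predicts.

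**The case against.** The strongest reply is that this is shorthand. The article refers to a detailed SAP for the methods, and a condensed account may say that the same method is used for another outcome without repeating each covariate. The secondary sections do adapt more than the response: MF-VEP has its own threshold and segment rule, and MTR has a different unit and an interaction term. The literal MTR model fits so poorly that it was probably not intended. This stands to the extent that the text does not show which model will be run. It does not dispose of the point, because the article states both a covariate by name and a substitution rule, and together they give the wrong model.

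Three stronger readings are tempting and are not supported.

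- *The secondary comparisons are biased.* Allocation is randomised, so leaving out own baseline causes no bias on average. The shift in step 5 of the working is conditional on a chance imbalance, which the documents cannot quantify.
- *The models amount to unadjusted change scores.* Against a wholly unadjusted change score, own-baseline adjustment has variance (1 + c)/2, that is 25%, 15% and 5% lower at c = 0.5, 0.7 and 0.9. That comparator overstates the loss for MF-VEP, where P100 is a latency from the same eye and may recover part of the adjustment.
- *Baseline MTR is ignored throughout.* The second MTR analysis groups lesions by it, so own baseline enters there, if coarsely.

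The exploratory visual outcomes are a weaker case, because their section lacks the replacement wording.

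**Conclusion.** The point holds as a defect of wording with a real, modest consequence. As written, the MF-VEP and lesional MTR models take over the baseline P100 covariate and name no own-baseline term. For MTR, neither that covariate nor the eye-level nesting can be applied to lesions without a decision that the article does not make. The gap is fullest for MF-VEP and for MTR by location.

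What is lost is precision and the correction of chance imbalance in the outcome's own baseline. On the assumed correlations, own-baseline adjustment would cut the variance of the treatment estimate by about 1–4% at r = 0.2, 11–25% at r = 0.5 and 26–49% at r = 0.7. These ranges rest on values that no document supplies. The primary analysis and every stated figure are unaffected.

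**What to change.** In the multifocal VEP and lesional MTR sections, state that the dependent variable and the baseline covariate are both those of the outcome analysed:

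- MF-VEP: baseline MF-VEP latency of the eye, with eyes nested within participants.
- Lesional MTR: baseline MTR of the lesion, with lesions nested within participants and no P100 term.

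Confirm the same principle for the exploratory visual outcomes in section {20b}, using the screening value for OCT, where change is measured from screening.

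If the SAP already specifies this, only the article's wording needs correcting. If the SAP repeats the article's rule, amend it before the secondary analyses are run, so that the covariate is not chosen with results in view. The cost is one clause per section: Table 2 already schedules multifocal VEP and MRI at baseline, so no new data are needed.

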### Secondary efficacy analysis: change in lesional MTR

The secondary (MRI) outcome measure is the change in lesional MTR, between baseline and week 26, for the lesions stratified by location or by tissue-specific cohort baseline lesional MTR values.

Analyses will be presented for change in lesional MTR for MS lesions grouped according to each location as follows: periventricular, deep white matter, juxtacortical, leukocortical, cortical grey matter, deep grey matter, mixed deep grey matter and white matter, brainstem and cerebellar lesions. Based on previous research [27], we hypothesise that the clearest effect will be seen in grey matter and brainstem lesions. We will apply the same method as applied for the primary outcome measure, with the dependent variable replaced by the change in lesional MTR for each lesion location subgroup. An interaction term will compare treatment group differences between lesion locations.

Analyses of change in lesional MTR stratified by cohort baseline lesional MTR values will be applied using the same method as the primary outcome measure with the dependent variable replaced by the change in lesional MTR for lesions: (1) grouped as being above or below the cohort median lesion MTR and (2) grouped into quartiles based on the baseline cohort lesion MTR. In line with previous research [27], the interaction test between treatment effects in different lesional groups will be a variable of key interest.

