### Sample size {14}

The primary endpoint is the change in the P100 latency of the VEP between baseline and week 26 for each eligible eye. An average reduction of 3.0 ms/eye in VEP at week 26 between metformin + clemastine (research arm) and placebo (control arm) will be an important treatment effect to detect. There is no evidence for an interaction of VEP between eyes. With a 5% significance level (two-sided), 80% power, and a common standard deviation of 5 ms, 45 eyes in each arm are required to detect a difference of 3.0 ms/eye in the mean change of VEP at week 26 from baseline between the two treatment groups (nQuery). The common standard deviation of 5 ms was based on the ReBUILD study [23], which was approximately 4.1 ms, and added around 20% (4.1 × 1.20 = 4.92) more variation. Allowing for 10% non-compliance, that is 50 eyes per arm: it was originally planned to recruit 50 participants. Following the planned interim analysis meeting held on 28/06/23, the trial sample size increased to 70 participants as around 50% of participants had only one eligible eye at screening. The Independent Data Monitoring Committee (IDMC) supported the plan to increase recruitment to reach the required eligible eyes.

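### The lesional-MTR interaction tests inherit a participant random effect only, so if lesions are the rows, participant-by-lesion-group variation is left out of their standard error

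*Protocol article*

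**What the plan says.** The section on the primary outcome measure (full-field VEP) sets a mixed model at eye level: "with random effects for participants and fixed effects for treatment allocation at randomisation, baseline P100 latency and stratification factors". No other random term is named. With at most two eyes per participant and no slope mentioned, the participant term is naturally read as an intercept.

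The section on change in lesional MTR carries this over: "We will apply the same method as applied for the primary outcome measure, with the dependent variable replaced by the change in lesional MTR". The analysis is done for each of nine lesion locations, and then "An interaction term will compare treatment group differences between lesion locations". Lesions are also split by baseline MTR, into halves at the cohort median and into quartiles. For these, "the interaction test between treatment effects in different lesional groups will be a variable of key interest". The section names no participant-by-location or participant-by-MTR-group term, no random slope and no cluster-robust variance.

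Randomisation is by participant, 1:1, with 70 participants planned (Sequence generation; Sample size).

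**The concern.** The primary model tests a treatment main effect, with both treatment and its random term at participant level. That is sound. The interaction asks a different question: does the difference between lesion groups inside a participant vary by arm? A participant intercept shifts all of that participant's lesions equally and drops out of the difference. The model is then left with lesion-level residual noise, averaged over all lesions, as its yardstick.

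Participants may differ in how their lesion groups change relative to one another, through biology or through tissue-dependent scanning and segmentation effects. That variation is shared by all of a participant's lesions in a group and does not average out as lesions are added. A model that omits it treats lesions as independent replicates of a contrast that has only about 70 independent units.

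The Discussion says the MTR analyses were tuned to more demyelinated and grey-matter lesions. It also regards agreement between imaging and electrophysiology as the most compelling evidence in the preceding trial. A spurious interaction would feed into that reading.

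**Working it through.** **The plan's only figure.** "With a 5% significance level (two-sided), 80% power, and a common standard deviation of 5 ms, 45 eyes in each arm are required". For a 3 ms difference, the normal approximation gives 2 × (1.960 + 0.842)² × 5² / 3² ≈ 43.6, so 44. The two-sample t calculation gives 45 (power 80.4%; 44 gives 79.5%), and 45 / 0.9 = 50. The figure reproduces, but it concerns the primary endpoint. No error rate or power is stated for the MTR interactions.

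**Inputs.** From the article: 70 participants at 1:1, so 35 per arm; two-sided 5%, borrowed from the primary; two, four or nine lesion groups. Assumed: m lesions per group per participant, and ρ, the share of lesion-level variance (after the participant intercept) that is participant-by-group.

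**Formula, two groups.** Write a lesion's change as participant effect u + participant-by-group effect v + lesion error e, with var(v) = ρσ² and var(e) = (1 − ρ)σ².

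- The participant's between-group difference has true variance 2(ρσ² + (1 − ρ)σ²/m); u has cancelled.
- The intercept-only model works with about 2σ²/m.
- The ratio is DE = 1 + (m − 1)ρ.
- Actual type I error = 2 × (1 − Φ(1.96/√DE)).

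The number of participants cancels, so a larger trial would not cure this.

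**Worked cells.**
- m = 20, ρ = 0.05: DE = 1.95, 1.96/1.396 = 1.404, giving 16.0%.
- m = 40, ρ = 0.10: DE = 4.90, 1.96/2.214 = 0.885, giving 37.6%.

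| Lesions per group | ρ = 0 | ρ = 0.02 | ρ = 0.05 | ρ = 0.10 |
|---|---|---|---|---|
| 2 | 5.0% | 5.2% | 5.6% | 6.2% |
| 5 | 5.0% | 5.9% | 7.4% | 9.8% |
| 10 | 5.0% | 7.1% | 10.4% | 15.5% |
| 20 | 5.0% | 9.5% | 16.0% | 25.0% |
| 40 | 5.0% | 14.2% | 25.4% | 37.6% |

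**Simulation, balanced.** With 35 per arm and 4,000 null runs per cell, m = 20 gave 9.8%, 16.8% and 26.1% at ρ = 0.02, 0.05 and 0.10. With m = 40 the results were 13.2%, 26.3% and 38.2%. Both rows agree with the table.

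**Simulation, uneven lesion counts.** A random-intercept model was fitted by REML to 70 participants. Counts were negative binomial, the participant intercept took 10% of variance, and baseline and stratification covariates were left out (1,000 null runs; 600 for nine groups, with an assumed mix of locations). Here the share is of total variance. With a mean of 40 lesions per participant in all:

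| Groups | share 0 | 0.02 | 0.05 | 0.10 |
|---|---|---|---|---|
| 2 | 4.4% | 12.9% | 21.3% | 39.6% |
| 4 | 5.1% | 12.8% | 25.3% | 40.6% |
| 9 | 4.2% | 9.5% | 18.3% | 35.2% |

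With a mean of 20 lesions and a share of 0.05, the results were 15.7%, 14.1% and 10.0% for two, four and nine groups.

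**After the fix.** In the two-group runs, comparing arms on each participant's between-group difference held type I error at 3.6% to 5.9% throughout. The random-effect version of the fix was not simulated.

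**The case against.** The best reply is that the article does not spell out the interaction model. The carried-over method is described for each location separately, and there a participant random effect deals with the clustering. The interaction comes in its own sentence. The carry-over is plainly shorthand, since read literally it would adjust MTR for baseline P100 latency. A separate SAP exists and may add a term. Nor does the article say that rows are lesions: with one mean per participant per group, m = 1 and DE = 1, so there is no inflation.

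Much of this stands as a limit. The row unit is inferred, and the SAP could already contain the right term. It does not dispose of the point, because the text gives a method for these analyses, with one random term, and then asks that method to support a contrast it does not suit. That is more than an omitted detail.

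A reader might go further and infer that the MTR interval is certainly too narrow, or that a false claim of location-dependent or integrity-dependent remyelination is likely. The documents do not support either. With no participant-by-group variance the test is close to nominal, and with few lesions per group, plausible for some of the nine locations, the inflation is slight. Even the worst cell in the closed-form table is 38%. Nor does the fault argue against the median and quartile groupings. Replacing them with continuous baseline MTR would be a preference that does not follow from the random-effects argument.

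Finally, these are secondary analyses in a phase 2a trial, and the Discussion itself treats all outcome measures in the field as exploratory. The label of key interest closes the baseline-MTR paragraph; the location interaction does not carry it explicitly.

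**Conclusion.** The point holds conditionally. Followed as written with lesions as rows, the interaction tests omit participant-by-lesion-group variation from their standard error. Whether this is trivial or serious turns on two quantities that the article does not give: lesions per group and the share of variance that is participant-by-group. Under the assumptions shown, the error rate runs from nominal to several times 5%. Inflation grows with lesions per group, so for a given share the median split, which pools all lesions into two groups, is more exposed than the sparser locations.

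The fault is confined to the interaction tests. It is worth correcting because these tests carry the interpretive weight of the MTR outcome and the correction is cheap.

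**What to change.** In the pooled lesion models that test the interactions, state that lesions are the rows and add a participant-by-lesion-group random effect to the participant intercept. For the nine locations a single variance component is enough; a full set of random slopes may not be estimable in 70 participants. Use small-sample degrees of freedom. For the median split, an equally good choice is to compare arms on each participant's difference between the two group means. Keep the pre-specified median and quartile groupings and the location list.

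If the SAP already has such a term, one clarifying sentence is enough. If not, make a dated SAP amendment. The Trial status section puts the start of analysis in April 2025, so if analysis has begun, report the corrected test beside the stated one and label it as added.

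The cost is wording and code, with somewhat wider intervals where the variation is real. If there is none, the component shrinks towards zero and little is lost. The participant-level version also drops anyone without lesions in both groups.

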### Interim analyses {21b}

The IDMC will review data, by treatment group, on the safety of participants in the trial. The IDMC will meet at least once a year, or at the frequency requested by the IDMC, until the end of the trial. There are no plans to stop the trial early for efficacy; therefore, there are no interim analyses for efficacy or futility. Efficacy data, by treatment group, will therefore not be routinely provided. The IDMC can request efficacy data, by treatment group, confidentially from the TSC if changes to the protocol are considered and these data are required by the IDMC to reach decisions about the ongoing risk/benefit to participants in the trial.

As described in the sample size section above, one pre-planned interim analysis was undertaken to review the sample size after the first 20 participants had completed their trial participation. It was through this mechanism that the sample size was increased from 50 to 70 participants (as approximately 50% of screened participants had only one eligible eye at screening).

